## Abstract

**Background:**

A novel evidence-based Narrative e-Writing Intervention (NeW-I) has been developed and tested in Singapore to advance psychosociospiritual support for parents of children with chronic life-threatening illnesses. NeW-I is informed by an international systematic review and a Singapore-based qualitative inquiry on the lived experience of parental bereavement and supported by literature on anticipatory grief interventions for improving the holistic well-being of parent caregivers of seriously ill children.

**Objective:**

This study's aim was to provide an accessible platform, NeW-I—which is a strengths- and meaning-focused and therapist-facilitated mobile app and web-based counseling platform—that aims to enhance quality of life, spiritual well-being, hope, and perceived social support and reduce depressive symptoms, caregiver burden, and risk of complicated grief among parents of children with chronic life-threatening illnesses.

**Methods:**

The NeW-I therapist-facilitated web-based platform comprises a mobile app and a website (both of which have the same content
and functionality). NeW-I has been implemented in Singapore as a pilot open-label randomized controlled trial comprising intervention and control groups. Both primary and secondary outcomes will be self-reported by participants through questionnaires. In collaboration with leading pediatric palliative care providers in Singapore, the trial aims to enroll 36 participants in each group (N=72), so that when allowing for 30% attrition at follow-up, the sample size will be adequate to detect a small effect size of 0.2 in the primary outcome measure, with 90% power and two-sided significance level of at least .05. The potential effectiveness of NeW-I and the accessibility and feasibility of implementing and delivering the intervention will be assessed.

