The overarching goal of the novel NeW-I intervention model is to provide an accessible platform for parent caregivers to reflect on their experiences of caring for a child with a chronic life-threatening illness from a new perspective (ie, new eye) as well as to create a renewed sense of self-understanding and empowered identity in the context of their experience (ie, new I). The specific research objectives are three-fold: (1) to develop a standardized protocol for a cultural-specific and meaning-oriented NeW-I for anticipatory grief and bereavement support for parent caregivers of children with chronic life-threatening illnesses and eventual death; (2) to evaluate the efficacy of NeW-I in enhancing quality of life, spiritual well-being, hope, and social support as well as decreasing caregiver burden, depressive symptoms, and risk of complicated grief among parent caregivers; and (3) to examine the challenges and pitfalls in the design and implementation of NeW-I through an integrated feasibility and acceptability study for informing large-scale implementation of the intervention.

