### Sample Size Calculation

For a main trial designed with 90% power and two-sided significance level of at least .05, a pilot sample size of 25 per arm is needed to detect a small effect size of 0.2 in the primary outcome measure [55]. A meta-analysis suggested that many high-quality psychotherapy studies (high quality studies defined by a proficiently trained therapist, treatment integrity, N>50) on the treatment of depression have a mean effect size of 0.22 [56]. Allowing for an attrition rate of 30% at follow-up (a larger estimate due to end-of-life context), the sample size must be inflated by a factor of 1/(1−0.3)=1.43. Therefore, the minimum sample size required for this study was 72 or 36 in each group.

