### Data Analysis

#### Quantitative Data

The statistical analysis plan for the quantitative data in this study was designed according to the Consolidated Standards of Reporting Trials guidelines [64] and recommendations made by Gamble et al [65] for clinical trials. Quantitative parameters will be presented as mean (SD) or median (IQR), and categorical variables will be presented as numbers and proportions. The internal consistency of psychometric scales will be assessed using Cronbach alpha. To compare the primary quantitative outcome (KQOL) and secondary quantitative outcomes (FACIT-Sp-12, HHI, PHQ-9, BSFC-s, ISS, and BGQ) between the intervention and control groups over time (time point 1 to time point 5, with time point 2 being the primary time point of comparison), multilevel mixed-effect regression analysis will be used with time as a random effect. All demographic and other relevant covariates measured at baseline will be adjusted in the model. Mixed models allow us to include all available data in the presence of dropouts occurring into the analysis [66]. Individual multivariable models will be constructed for each outcome to estimate the effect sizes and corresponding CIs. Clinically meaningful interactions will also be checked and included in the model if *P*<.10. Marginal effects will be used to predict mean outcome scores for the intervention and control groups. For this study, a two-sided significance level of at least .05 will be considered a statistically significant finding. All analyses will be conducted using Statistical Package for the Social Sciences (SPSS) (version 22.0; IBM Corp) and Stata (version 15.1; StataCorp) statistical software.

The intention-to-treat principle will be followed in the data analysis. However, an additional sensitivity analysis will be conducted to handle missing data during the analysis, where fully conditional multiple imputation with *n (% missing)* imputations and 1000 iterations using the Markov Chain Monte Carlo method will be used [67]. Model summary estimates will be calculated based on the Rubin rule [68].

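### The Abstract credits this pilot with 90% power for an effect of 0.2, but the 90% belongs to a future main trial; the pilot's own power is roughly 10-30%

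*Protocol article*

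**What the plan says.** The Abstract (Methods) sets enrolment at 36 per group, N=72, and says that after 30% attrition "the sample size will be adequate to detect a small effect size of 0.2 in the primary outcome measure, with 90% power". The sentence names this trial's enrolment, attrition and primary outcome, so it is a claim about this trial's own power.

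The Sample Size Calculation section starts from a different place: "For a main trial designed with 90% power and two-sided significance level of at least .05, a pilot sample size of 25 per arm". The power figure there describes the main trial, and 25 per arm is the pilot's size. The same sentence then runs the two together, since it reads "a pilot sample size of 25 per arm is needed to detect a small effect size of 0.2 in the primary outcome measure". In support it cites a meta-analysis in which high-quality psychotherapy studies "on the treatment of depression have a mean effect size of 0.22". The 25 is then divided by 0.7 for attrition, giving 36 per arm.

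The article calls the study a pilot that will inform a full-scale protocol (Abstract; Discussion, Research Synopsis and Implications). Yet the second research objective is "to evaluate the efficacy of NeW-I in enhancing quality of life, spiritual well-being, hope, and social support", among other outcomes. The Quantitative Data section names time point 2 as the primary comparison, plans a covariate-adjusted mixed model with effect sizes and CIs, and states that "a two-sided significance level of at least .05 will be considered a statistically significant finding".

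**The concern.** The two sections give the same 90% to two different trials. If the Abstract is taken at its word, a null result on quality of life would count as good evidence against an effect of 0.2. If the pilot's own power is far lower, a null result says almost nothing about an effect of that size. A significant result would then need an observed difference well above 0.2, if the true effect is near 0.2. Either could mislead the planning of the full-scale trial, which is what the pilot is for.

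**Working it through.** **Inputs.** From the article: effect size 0.2 (and 0.22 as support), two-sided alpha .05, 25 evaluable per arm, 30% attrition, 36 per arm enrolled, equal allocation, primary comparison at time point 2. The article gives no SD for the Kemp Quality of Life scale and no within-person correlation. I therefore read 0.2 as a difference in SD units and show correlations as assumed ranges.

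**1. The headcount reproduces.** 25 / (1 − 0.3) = 35.7, rounded up to 36 per arm, so N=72.

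**2. The 90% power does not.** Normal approximation: power ≈ Φ(d·√(n/2) − 1.96).

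- n = 25: 0.2 × √12.5 = 0.707; Φ(0.707 − 1.96) = Φ(−1.253) = 10.5%. Noncentral t: 10.7%.
- n = 36: 0.2 × √18 = 0.849; Φ(0.849 − 1.96) = Φ(−1.111) = 13.3%. Noncentral t: 13.3%.
- With d = 0.22 (noncentral t): 11.9% at 25 and 15.1% at 36.

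**3. Allowing for baseline adjustment.** With correlation r between baseline and time point 2, the effective difference is d / √(1 − r²). For r = 0.5 it is 0.2 / 0.866 = 0.231; for r = 0.8 it is 0.2 / 0.6 = 0.333.

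| Evaluable per arm | Unadjusted | r = 0.5 | r = 0.7 | r = 0.8 |
|---|---|---|---|---|
| 25 | 10.7% | 12.6% | 16.3% | 21.1% |
| 36 | 13.3% | 16.2% | 21.6% | 28.6% |

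Reaching 90% this way would need r of about 0.98 (25 per arm) or 0.97 (36 per arm).

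**4. What 90% power would require.** n per arm = 2(1.960 + 1.282)² / 0.2² ≈ 526 by the normal approximation, or 527 by the t test, all evaluable. That is 527 / 25 ≈ 21 times the planned number. Turned round, the unadjusted effect detectable with 90% power is 0.94 SD at 25 per arm and 0.77 SD at 36.

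**5. Precision and the significance threshold.** The unadjusted 95% CI half-width is t × √(2/n) in SD units. At 25 per arm it is 2.011 × 0.283 = 0.57; at 36 it is 1.994 × 0.236 = 0.47. The observed difference must exceed the same figure to be significant, which is 2.4 to 2.8 times the design effect of 0.2.

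**The case against.** **The sizing section is the operative one, and it is about a pilot.** This stands. That section opens with the main trial, its inflation step is correct, and nothing in the article shows 72 to be a poor pilot size. A reader might infer that the trial is too small and must recruit more. The article does not support that: the fault is that the main trial's power has been moved to the pilot.

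**A flat 11% is too exact.** This also stands. It fits only an unadjusted comparison of 25 per arm. The planned model is adjusted for baseline covariates, and the 30% attrition is at follow-up, which runs to 6 months after completion. More than 25 per arm may therefore be available at time point 2. A range is the honest statement, but no part of it comes near 90%. Even averaging all four post-baseline assessments with baseline adjustment (assumed correlations 0.5 to 0.8) gives only 21-33% at 25 per arm and 28-45% at 36, and that is not the named primary comparison.

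**The 0.2 might be Cohen's f for a group-by-time interaction.** With N=50 and correlation 0.5 this would give 79% (two time points) to 96% (five). It is the only reading tried that reaches about 90%. The article does not state it, and it fits poorly with the description of 0.2 as small, with the supporting mean effect of 0.22 and with the primary comparison at a single time point.

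**Any significant result must be greatly exaggerated.** A reader might infer this too, but it holds only if the true effect is near 0.2. The article does not establish the true effect on quality of life; the 0.22 comes from treatment of depression.

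**The article already hedges.** It speaks of potential effectiveness, plans CIs, and leaves evaluation of efficacy to further research. This is partly right, and it means that barring P-value conclusions altogether would be a preference rather than a correction. But the second objective and the hypotheses are still worded as efficacy claims.

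**Conclusion.** The Abstract's power statement is wrong as written and contradicts the Sample Size Calculation section. At a standardised difference of 0.2 and two-sided .05, this trial's own power at time point 2 is about 11% (25 evaluable per arm) to 13% (36 per arm) unadjusted. With baseline adjustment it is roughly 13-29%, assuming correlations of 0.5 to 0.8, which the article does not give. If the true effect is near 0.2, a null result is uninformative. The finding is against the claim, not against N=72.

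A separate and minor slip is the phrase "two-sided significance level of at least .05", which appears in the Abstract, the Sample Size Calculation section and the Quantitative Data section. Read literally it sets a floor on the type I error. The natural reading is the conventional .05, so it should not be taken as a sign that error control was abandoned, and it has no part in the power error.

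**What to change.** 1. **Abstract, Methods.** Say that N=72 is a pilot size (25 per arm, inflated for 30% attrition) preceding a main trial designed with 90% power for an effect of 0.2. Remove the claim that this trial has that power. Do not add a reason for the choice of 25 that the article does not give.
2. **Sample Size Calculation.** Delete the words that make the pilot's 25 per arm a number needed for detecting 0.2. State the pilot's own power at 0.2 as roughly 10-30% depending on assumptions, or state its expected precision (unadjusted 95% CI half-width about 0.57 SD at 25 per arm).
3. **This Study and Objectives.** Describe the second objective as obtaining preliminary estimates of effect. Present the time point 2 difference in quality of life with its 95% CI as the main result; CIs are already planned.
4. **Minor.** In all three places, give the two-sided significance level simply as .05.

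The cost is wording only, with no extra participants and no change to data collection. The stated power becomes much less favourable.

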**Results:**

Funding support and institutional review board approval for this study have been secured. Data collection started in January 2019 and is ongoing.

**Conclusions:**

NeW-I aspires to enhance holistic pediatric palliative care services through a structured web-based counseling platform that is sensitive to the unique cultural needs of Asian family caregivers who are uncomfortable with expressing emotion even during times of loss and separation. The findings of this pilot study will inform the development of a full-scale NeW-I protocol and further research to evaluate the efficacy of NeW-I in Singapore and in other Asian communities around the world.

**Trial Registration:**

ClinicalTrials.gov NCT03684382; https://clinicaltrials.gov/ct2/show/NCT03684382

**International Registered Report Identifier (IRRID):**

DERR1-10.2196/17561

## Introduction

### Background

There is a global increase in the number of children living with chronic life-threatening illnesses [1,2]. In Singapore, child deaths (age <19 years) due to chronic conditions increased from 204 per year to 245 per year during the 2014 to 2016 period [3]. In fact, congenital anomalies as well as cardiovascular and cerebrovascular diseases account for over half of all deaths in the 0 to 19 years age range in Singapore [4]. Due to technological developments in medical care, children with chronic life-threatening illnesses can live longer, but they simultaneously face the challenge of being dependent on their caregivers (usually, their parents) and disability for a prolonged period [1]. However, not all seriously ill children and their parents receive adequate palliative support services [3].

Being a parent caregiver of a child with a chronic life-threatening illness is a highly stressful experience [5]. In addition to the typical challenges of parenting, parent caregivers must navigate a complex web of stressors, including the practical and financial burden of caregiving [6], strained marital and social relationships [7], and neglect of other healthy children and family members [8]. Furthermore, parent caregivers of children with chronic life-threatening illnesses need to frequently communicate and engage with medical professionals, but such interactions can increase the anxiety and distress of the parents if they are not adequately involved in making decisions regarding their child’s treatment [9,10]. Thus, the stressors associated with caregiving and the elevated demand on resources put parent caregivers at increased risk of depressive symptoms, fatigue, and overall poor quality of life [11].

### Parental Bereavement Trajectories of Child Loss

Our research team recently conducted a qualitative systematic review of 25 high-quality research papers published between 2000 and 2017, exploring the lived experience of parental bereavement due to a child’s chronic life-threatening illness. A 4-phase parental bereavement trajectory of child loss was developed, highlighting appropriate interventions that help parents identify care needs, elicit caregiving strengths, enhance death preparedness, and foster meaning-making throughout the trajectory of their child’s illness to reduce psychoemotional distress during the period of end-of-life caregiving and into bereavement [12]. Our research team conducted a second study to examine the Asian experience of parental bereavement via meaning-oriented strength-focused interviews with 6 couples, 13 mothers, 4 fathers, and 2 primary parental figures (N=25 parental units) who lost their child to a chronic life-threatening illness in Singapore [13,14]. Grounded theory analysis revealed 7 themes and 25 subthemes that were organized into a trauma-to-transformation model of parental bereavement (Figure 1). This culture-specific model shows the milestones of how Asian bereaved parents journeyed through their child’s life-threatening illness and eventual death, describing the ritualistic actions as well as family communication and transactional patterns that aided them to better cope with their loss, to regain control over their lives, to sustain a continuing bond with their deceased child, and to move forward with and ultimately transcend their grief through meaning reconstruction [13,14].

**Figure 1 figure1:**
[figure not shown]
Trauma to transformation model of parental bereavement in Asia.

These findings echo previous literature [15-18] positing that parents facing potential child loss could benefit from psychosocial and therapeutic interventions as soon as prognosis is known and throughout the trajectory of the illness, which could ease the transition from caregiving through mortality and bereavement, thus mitigating adverse grief outcomes (Table 1). However, most supportive interventions for parents caring for children with chronic life-threatening illnesses only occur after bereavement [19-21], and a recent systematic review found negligible evidence to support their effectiveness [22]. As such, there is a need to develop a preloss intervention to augment pediatric palliative care and parental bereavement support service—one that empowers parents to reflect on their caregiving experiences, explore and identify resources that could help them better cope with the challenges of caregiving, and support their child to live a meaningful life despite a chronic life-threatening illness.

**Table 1 table1:** Clinical implications of findings from the qualitative study on the lived experience of parental bereavement in Asia.

Findings from qualitative studies on the lived experience of parental bereavement in Asia	Implications for clinical work
Facing their child’s impending mortality is a difficult experience, which can isolate parents. Societal attitudes toward illness can make it difficult for parents to engage with their previous social networks.	Support parents in gaining a greater sense of control over their lives and strengthening resilience during the period of end-of-life caregiving through empathic support and psychoeducational resources for self-care and healthy coping.
Parents seek to understand the medical terminology associated with their child’s illness and prognosis of the condition, so that they can evaluate potential risks and benefits of treatment procedures and make informed care decisions.	Empower parents to provide the best possible care to their child through exploration of resources for seeking information about illness and caregiving.
Parents desire to give their children a chance to rise above the difficulties brought on by the illness and display strength to help their child live as fully as possible.	Facilitate meaningful family experiences that allow parents and their children to move away from the drudgery of illness, suffering, and caregiving and focus on building parent-child memories.
Asian parents tend to have a collaborative approach to caregiving for their sick child. They often rely on family members, relatives, and other parents of sick children for support.	Explore sources of support, which participants have within their close social network and how they can be harnessed in care provision.

### Elements of a Preloss Intervention for Parents of Children With Chronic Life-Threatening Illnesses

In developing a preloss intervention that could meaningfully impact families throughout their child’s trajectory of illness and leading to the final days of their child’s life, a number of important therapeutic elements need to be considered and incorporated. First, anticipatory grief, defined as the process of mourning the loss of a loved one before actual loss that enables caregivers to experience and adjust to various grief responses, must be central to such an intervention [17,23]. Anticipatory grief can smoothen the process of coping with death as the individual has the scope to come to terms with the loss in advance [24]. Studies have found that strength-based end-of-life interventions with elements that address anticipatory grief can improve adult patients’ quality of life and mitigate poor bereavement outcomes among family caregivers [25]. It is, therefore, possible that an anticipatory grief-based psychotherapeutic intervention for parents of children with chronic life-threatening illnesses could help parents to understand and regulate their emotions, enhance death preparedness, and thereby build resilience.

Second, it would be useful for a preloss intervention for parents of children with chronic life-threatening illnesses to adopt a meaning reconstruction approach [26-28], with each individual actively constructing a phenomenological world of their experiences in relation to various familial and sociocultural contexts and supporting their sense of loss and grief accordingly. Such a meaning reconstruction approach empowers grievers to choose whether to direct their attention to the loss and process turbulent feelings or to focus on practical adjustments to re-engage with their everyday life. Third, a preloss intervention would benefit from a narrative approach [29,30], which could help individuals connect with emotions that are challenging to accept, generate new meaningful stories about life and loss, and restructure negative emotional appraisal of situations such as end-of-life caregiving into more positive ones, thereby generating a sense of hope.

Two effective examples of applying the meaning reconstruction approach and the narrative approach in supporting holistic end-of-life care are dignity therapy [25,31,32] and family dignity intervention [33]. Both of these are evidence-based psychotherapies that address the physical, psychosocial, and existential issues pertaining to one’s dignity at the end-of-life period. Specifically, a family dignity intervention is designed to support the collective experience of grief and loss for Asian families facing mortality, and it could add great value to a preloss intervention for parents of children with chronic life-threatening illnesses. In practice, family dignity intervention comprises a meaning-focused interview with a patient-and-family caregiver dyad that fosters the expression of appreciation and emotional connection through the retelling of important life narratives. The interview is recorded, transcribed, and edited into a legacy document and returned to the dyad for sharing with their loved ones for healing and remembrance.

Finally, a preloss intervention for parents of children with chronic life-threatening illnesses must be mindful of the caregiving responsibilities and limitations that serve as barriers for parents to engage in sit-and-talk therapy [12]. It is possible that a web-based platform that is cost-effective and time-efficient [34] can deliver psychotherapy to such parents. Such therapist-facilitated internet-based platforms are increasingly used for brief and effective psychotherapy for a range of conditions, including depression, anxiety, and stress [35-40]. Moreover, when web-based platforms use writing as the modality for emotional expression and reflection, efficacy is superior compared with audio or video mediums [41]. Finally, the anonymity of an e-writing channel can encourage greater willingness to self-disclose [42,43].

